## Abstract

**Background:**

The prevalence of hypertension is increasing worldwide. Hypertension self-management usually involves the application and consideration of oral, written, or quantitative information. Hypertensive patients in China have limited high blood pressure health literacy (HBP-HL), which may lead to poorer clinical outcomes. This study aims to determine the feasibility and effectiveness of an interactive pictorial health education program based on behavior change wheel (BCW) theory and its effect on HBP-HL, self-efficacy, self-management ability, and health-related quality of life (HRQOL) in hypertensive patients with low HBP-HL.

**Methods:**

This study is a randomized controlled trial (RCT). One of the municipal districts in Huzhou, China, will be randomly selected, and two communities with similar conditions within this district will be screened and selected. A total of 120 hypertensive patients aged 18 years and older will be recruited from these two community settings. One of the communities will be randomly allocated to an interactive pictorial health education program conducted by a comprehensive health literacy strategy that includes (i) training participants in effective health communication skills that address issues encountered in seeking medical care and (ii) the use of self-developed interactive pictorial hypertension education to improve patient understanding and behaviors versus a control group (routine community lecture health education only). The primary outcome measure is HBP-HL. Secondary outcomes are self-efficacy, self-management ability, HRQOL, social support, and improvement in blood pressure. Outcomes will be collected at 6, 9, and 12 months from trial entry.

**Discussion:**

The strengths of this study are the establishment of a new health management program for hypertensive patients that closely combines BCW theory and health literacy. This trial has the potential to improve HBP-HL in hypertensive Chinese patients with low health literacy to improve the self-management of hypertension and help control blood pressure.

**Trial registration:**

Clinical Trials.gov Protocol Registration and Results System ID NCT04327102. Prospectively registered on February 29, 2020

## Strengths and limitations of this study

The main strength of the study lies in establishing a new health management program for hypertensive patients combining BCW theory and HBP-HL closely to better address the problem under study.Further strengths are that we will match the intervention and control cases in order to reduce bias and confounding factors as much as possible as well as the fact that data are collected in a naturalistic situation.One limitation is that the trial is not double-blinded and will be implemented in only two communities.Another possible limitation of this study is the short 9-month intervention and 3-month follow-up intervention, which may not be long enough to observe the effect of the intervention on the occurrence of hypertension complications.

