### Setting

The participants will be recruited from the community settings in Huzhou, Zhejiang Province, China. First, one of the municipal districts in Huzhou will be randomly selected, and then two communities with similar conditions within the district will be screened and selected. Finally, the two communities will be randomly allocated to the intervention group and the control group. Subjects meeting the inclusion criteria will be enrolled into the intervention group and the control group after informed consent is obtained. In addition, we will contact community health providers to participate in the study to ensure the cooperation of participants**.**

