### Randomization and blinding

#### Sequence generation

After completing the screening of the two communities with similar size, educational background and economic income, randomization will be performed at the level of the community after recruitment is completed. One community will be randomized to receive the intervention, and the other community will be randomized to the control group by throwing dice. The randomization process will be completed by a third party unrelated to the study. Only after the subjects have completed the baseline data collection, the allocation personnel can inform the researchers of the allocation results.

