### Statistical analysis

The SPSS 23.0 software will be used for data processing and statistical analysis. Descriptive statistics will be used to process sociodemographic data, of which observable variables are presented as the means ± standard deviations for continuous variables and frequencies and percentages for categorical variables. Exploratory analysis will be applied to examine the distribution of data. Baseline data comparisons between the two groups will be conducted using the chi–square (*χ*^2^) test (for categorical variables) and *t-test* or Wilcoxon rank-sum test (for continuous variables). 2(group)× 3(time) ANOVA is used for data with a normal distribution and homogeneity of variance, and a generalized estimation equation is used for data with a nonnormal distribution to determine the main effect of intervention factors, time factors, and interaction between group factors and time factors. Simple effects will be further analyzed when there are interaction effects. A two-tailed *P* < 0.05 will be considered statistically significant.

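### Matching of cases is claimed as protection against confounding, but the Methods describe only the choice of two similar communities, and the stated model does not control participant-level imbalance

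*Protocol article*

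**What the plan says.** Under Strengths and limitations, the article states: "we will match the intervention and control cases in order to reduce bias and confounding factors as much as possible".

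The Methods describe the following:

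- **Communities (Setting; Sequence generation).** "two communities with similar conditions within the district will be screened and selected". The criteria appear as "screening of the two communities with similar size, educational background and economic income", without tolerances. Then "One community will be randomized to receive the intervention, and the other community will be randomized to the control group by throwing dice".
- **Participants (Setting; Recruitment and study population).** "Subjects meeting the inclusion criteria will be enrolled into the intervention group and the control group after informed consent is obtained". Recruitment is by leaflet and by introduction from local providers, followed by an eligibility interview. No matching variable, ratio or pairing step is given.
- **Sample size calculation.** Independent groups and a two-sample t-test; 108 participants before dropout and 120 after.
- **Statistical analysis.** "2(group)× 3(time) ANOVA is used for data with a normal distribution and homogeneity of variance", with a generalized estimating equation for non-normal data. The effects named are group, time and their interaction. For baseline, "Baseline data comparisons between the two groups will be conducted using the chi–square" test, or a t or rank-sum test for continuous variables. No consequence is attached to the result.
- **Table 2.** C-HBP-HLS is measured four times (T0, T1, T2, T3). The analysis has three time levels and does not say which.

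**The concern.** The claim speaks of cases, which a reader takes to mean participants. Individuals are not randomised here: each person's arm follows from the community they live in. Participant matching would then be the main design safeguard against differences in age, education or starting health literacy between the arms, and a reader of the results would assume that it had been done. If it was not, such differences pass into the estimated effect while the report says they were dealt with.

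**Working it through.** The matching claim carries no figure to reproduce. The check sets the sections against each other and then sizes the consequence.

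**1. Is participant matching described?** Setting, Recruitment and study population, Sequence generation, Sample size calculation, Statistical analysis and Quality control were read for a matching variable, tolerance, ratio, pairing step or paired analysis. None is there. What is there is similarity of the two communities on three characteristics.

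**2. Where does a baseline imbalance go in the stated model?** Let D be a difference in mean C-HBP-HLS between the communities that is constant over time, and E the treatment effect, taken as equal at each post-baseline visit.

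| Three time levels | Group main effect | Interaction |
|---|---|---|
| T0 and two later visits | D + (2/3)E | post minus baseline: (D + E) − D = E |
| T1, T2, T3 | D + E | differences among post visits only: 0 |

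D is in the group main effect in both rows. In the first row the interaction removes a constant D. In the second row no stated effect removes it, so D is in the whole comparison. Group differences at a single post-baseline visit, which the simple-effects step may report, equal D + E in either case.

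**3. How much could D matter?** The documents give no D, so a range is assumed. Inputs: pilot SDs 4.89 and 4.78 (Sample size calculation), pooled SD = sqrt((4.89² + 4.78²)/2) = 4.835; 54 per arm (108/2); no true effect; unadjusted two-sided 5% test of a post score. The rejection probability is Φ(−1.96 + k·sqrt(54/2)) + Φ(−1.96 − k·sqrt(54/2)), where k is D in SD units.

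| k (assumed) | D in points | False-positive rate |
|---|---|---|
| 0.1 | 0.5 | 8% |
| 0.2 | 1.0 | 18% |
| 0.3 | 1.5 | 34% |
| 0.5 | 2.4 | 74% |

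These rates describe any uncontrolled difference. Adjustment addresses only the part carried by measured covariates.

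**4. What does baseline adjustment gain in precision?** Let r be the baseline-outcome correlation, assumed 0.5 to 0.7, with equal variance at both occasions.

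- Against a post-score comparison, the remaining variance is 1 − r²: 0.75 at r = 0.5 and 0.51 at r = 0.7. The cuts are 25% and 49%.
- Against a change-based contrast, whose variance factor is 2(1 − r), the ratio is (1 − r²)/(2(1 − r)) = (1 + r)/2: 0.75 at r = 0.5 and 0.85 at r = 0.7. The cuts are 25% and 15%.

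**5. If participants really were paired one to one.** With a within-pair correlation of 0.3 to 0.5 (assumed), ignoring the pairing overstates the standard error by 1/sqrt(1 − 0.3) = 1.20 to 1/sqrt(1 − 0.5) = 1.41. That errs on the conservative side.

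**The case against.** The best reply is that choosing communities alike in size, education and income is itself a form of matching, and that the word cases is loose wording for it. This stands in part. A reader might infer that no protection against confounding exists at all, and the documents do not support that: there is deliberate, if loose, community-level matching. But it does not match cases, and similar communities can still yield dissimilar volunteers.

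Second, this is an article. A covariate list is commonly left to the analysis plan, and the article does not exclude covariates. That also stands: the missing list is not the fault. The fault is a claimed safeguard that the article's own recruitment, sample size and analysis sections do not contain. Adjustment is proposed as the remedy.

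Third, a reader might infer that the planned analysis would be wrong if cases were matched. That holds only for one-to-one pairs, and then the inference is conservative. Frequency matching needs no paired test.

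Fourth, a reader might infer that a baseline imbalance always contaminates the result. If T0 is one of the three time levels, the interaction subtracts a constant imbalance. The article does not say whether it is.

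Finally, the graver weakness is one community per arm, which neither matching nor adjustment cures. That is true, and the article already lists the use of only two communities as a limitation. It does not excuse an unsupported claim of bias control next to it.

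**Conclusion.** The point holds in this form: the matching claim is not supported by the Methods, which describe selection of two similar communities and no matching of participants. Person-level imbalance is not controlled as claimed. It is in the group main effect whichever three visits are used, and in the whole comparison if they are T1 to T3.

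The size depends on quantities that the documents do not give. An uncontrolled difference of 0.2 to 0.3 SD, about 1.0 to 1.5 points, would raise the false-positive rate of an unadjusted post-score test from 5% to between 18% and 34%. The precision gain from baseline adjustment is 25% to 49% or 25% to 15% of residual variance, depending on the comparator, for r from 0.5 to 0.7. The point should be corrected, but it is not a flaw that adjustment can turn into a sound cluster comparison: unmeasured community effects stay confounded with treatment.

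**What to change.** - **Strengths and limitations.** Replace the claim with a statement that two communities similar in size, education and income were selected. If participants really are matched, state the variables and the rule, and reconcile the sample size and the analysis with them.
- **Statistical analysis.** Adjust the HBP-HL comparison for baseline C-HBP-HLS, age, gender and education, fixed in advance and kept whatever the baseline tests show. Name the three time levels. With baseline as a covariate, T1 to T3 as the outcome levels fits the existing three-level layout.
- **Limitations.** Add that adjustment covers only measured participant differences, and that with one community per arm unmeasured community effects cannot be separated from the intervention.

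The cost is wording and a few model terms. C-HBP-HLS and the sociodemographic items are already scheduled at T0, so no new data are needed. The price is that a claimed strength is scaled back.

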## Background

As one of the most common cardiovascular diseases in the world, hypertension has been proven to be a primary and independent risk factor for coronary heart disease, heart failure, stroke, and other cardiovascular and cerebrovascular diseases [1]. At present, complications of hypertension are the leading cause of death globally and are extremely common in many low- or middle-income countries, causing approximately 10.4 million deaths worldwide each year [2]. According to the American Heart Association (AHA), the number of deaths caused by hypertension and its complications will increase to more than 23.6 million by 2030 [3]. Research has shown that the number of hypertensive patients in China is 245 million (the prevalence rate is 23.2%), and it is still growing [4]. Due to the large number of hypertensive patients and the lifelong health care the condition entails, strengthening the health management of hypertension worldwide is urgently needed.

Health-related quality of life (HRQOL) is one of the main indicators used to evaluate the health management of hypertension [5]. Meanwhile, multiple studies have shown that health literacy is one of the main influencing factors for HRQOL in hypertensive patients and is positively correlated with HRQOL [6–8]. A completed cross-sectional investigation by our team confirmed that health literacy was the key influencing factor of HRQOL in hypertensive patients from Huzhou. In addition, health literacy is an independent predictor of blood pressure control and can predict patients' health outcomes better than sociodemographic data (age, income, occupation, education level and race) [9–11].

The American Institute of Medicine defines health literacy as “individuals’ ability to obtain, understand, and process basic health information and services needed to make appropriate health-related decisions” [12]. Nutbeam describes it as “interactive, functional and critical health literacy, reflecting a comprehensive ability” [13]. The literacy of chronic disease prevention and treatment was 15.71% among Chinese residents in 2017, an increase of 6.64% compared with 2012, but still at a relatively low level [14]. A 10-region prospective study in China showed that the prevalence of hypertension was highest in Zhejiang (44.4%) [14]. Only 6.83% of hypertensive patients have adequate health literacy [15]. Patients with inadequate health literacy lack disease prevention and health care knowledge and cannot search for information on health and self-management [16, 17]. They ultimately lose the best opportunity for prevention and treatment with an increased incidence of complications. Although their medical utilization is greatly reduced, the medical costs sharply increase [18, 19]. Studies show that people with low health literacy are 1.5–3 times more likely to have adverse health outcomes than those with high health literacy [20]. However, it is remarkable that intervention for patients with low health literacy can effectively improve their health status [9]. One of the most promising measures to achieve national health is to strengthen health education, improve health literacy, and enable patients with chronic diseases to learn related abilities of chronic disease management [21, 22].

It has been proven that providing materials or information on communication skills for people with low literacy can improve comprehension for patients with both low and high literacy [20, 23]. The “Conversation Map” is a very practical interactive health education tool launched by the International Diabetes Federation [24]. As an educational medium, pictures can lead patients to discuss with each other and realize a heuristic approach to answering questions. Different kinds of pictures have been adapted in health education for diseases such as stroke, bronchial asthma, and chronic heart failure [25, 26], which improves acceptance and meets the needs of patients with low health literacy. To date, very few studies have been specifically implemented to develop pictures and intervention strategies suitable for hypertensive patients with low health literacy to improve their health literacy. Addressing literacy through improved educational materials and intervention strategies is a potentially successful strategy. It is an innovative method to optimize patients’ understanding, improve their health literacy and HRQOL, and enhance their self-efficacy and self-management behaviors.

Studies show that intervention strategies based on the principle of behavior change are more robust, efficient, and practical [27, 28]. The BCW theoretical model (Fig. 1) [29] is a comprehensive behavior change system rooted in an integration of 19 behavior change frameworks. The wheel consists of three layers. At the center, the Capability, Opportunity, and Motivation model includes subjective factors (physical and psychological capability, automatic and reflective motivation) and objective factors (physical and social opportunity) and identifies the conditions required for behavior to occur and provides a method for formulating corresponding health management plans to promote healthy behavior change. The second layer is composed of nine intervention functions (Fig. 1), which are the general methods by which interventions might change behavior. The topmost layer of the wheel itemizes the policy categories that can be used to support the implementation of these functions.

**Fig. 1 Fig1:**
[figure not shown]
The behavior change wheel consists of three layers. The center layer is composed of the Capability, Opportunity, and Motivation model. The second layer is composed of nine intervention functions which are the general methods by which interventions might change behavior. Examples are “education” and “persuasion.” The topmost layer of the wheel itemizes the policy categories that can be used to support the implement of these functions

To address this problem, we intend to develop an interactive pictorial health education program based on the nine intervention functions of BCW theory, which is targeted to improve the health literacy and self-management capacity for hypertensive patients with low health literacy.

Our study attempts to answer two primary questions:(i)Is it feasible to use the interactive pictorial health education program based on BCW theory for application in the community setting? We hypothesize that hypertensive patients with low health literacy would be willing to participate in this program and would have high compliance, and there would be no adverse events occurring during the intervention.(ii)What are the impacts of interactive pictorial health education programs based on BCW theory on hypertensive patients with low health literacy? We hypothesize that participants receiving BCW-based interactive pictorial health education program interventions compared with a routine community lecture health education only group will demonstrate an improvement in HBP-HL, HRQOL, self-management ability, and self-efficacy and a reduction in blood pressure.

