### Outcomes and measuring instruments

#### Sociodemographic questionnaire

The questionnaire is a self-administered survey including age, gender, education, occupation, financial status, marital status, living condition, insurance status, smoking and alcohol status, history of hypertension, family history of hypertension, types of blood pressure medications, self-test blood pressure status, and complications.

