#### Feasibility

We will calculate the proportion of participants completing the intervention. Attendance will be examined as the proportion of participants who attend 9/11 sessions and the average number of sessions attended. At the end of each intervention session, a 5-point Likert scale (not at all to very much) will be used to rate all participants to gauge their level of satisfaction with the project and their mental and social engagement. At the 3-month follow-up assessment, participants will indicate their level of interest in participating in the project in the future and whether they would recommend it to others.

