	Chinese SF-36 Health Survey	√		√	√	√
	SBP	√		√	√	√
	NBP	√		√	√	√
	BMI	√		√	√	√
	NC	√		√	√	√
	WC	√		√	√	√
	hip perimeter	√		√	√	√
Sociodemographic data		√				

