### Dropouts and missing data

Reasons for dropouts will be documented and reported. If patients are alive and missing at random, we will use multiple imputation methods based on ten imputed datasets with multiple imputation by chained equations [37].

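### The feasibility hypothesis includes zero adverse events, but neither the feasibility measures nor the assessment schedule includes a way to ascertain them after baseline

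*Protocol article*

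**What the plan says.** At the end of the Background the article announces its aims with "Our study attempts to answer two primary questions". The first is feasibility in the community. Its hypothesis has three parts: patients will be willing to take part, they "would have high compliance, and there would be no adverse events occurring during the intervention".

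The Feasibility section then lists the measures. It begins "We will calculate the proportion of participants completing the intervention" and continues "Attendance will be examined as the proportion of participants who attend 9/11 sessions and the average number of sessions attended". After each session, "a 5-point Likert scale (not at all to very much) will be used to rate all participants", covering satisfaction and engagement. At the 3-month follow-up, participants are asked about future interest and whether they would recommend the project. None of these concerns adverse events.

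Table 2 lists the instruments at baseline (T0), 6 months (T1), 9 months (T2) and the 3-month follow-up (T3), down to hip circumference, with no event row. The only item that names clinical events is the last in the Sociodemographic questionnaire, which ends "self-test blood pressure status, and complications". In Table 2 the row "Sociodemographic data" is ticked at baseline only.

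Two other sections bear on the point. Recruitment and study population says that participants with adverse events during the intervention or follow-up are withdrawn. Dropouts and missing data says that reasons for dropout are documented and reported; the same section allows for deaths with "If patients are alive and missing at random".

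**The concern.** One of the three parts of a primary hypothesis has no matching measurement. The withdrawal rule presupposes that events are detected, but the article names no means of detecting them, and the dropout record holds only events that someone noticed and that ended participation. The Quality control section has community providers monitor recruitment, consent and the collection of measurements, not events. The monthly telephone calls fall in months 10 to 12, after the intervention period that the hypothesis covers.

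The hypothesis is also loosely fixed. It does not say whether any illness counts or only harm from the programme, or in which arm. The participants are hypertensive adults with at least one modifiable cardiovascular risk factor, so over 9 months the two readings could give very different answers.

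At stake is the meaning of the safety part of the feasibility conclusion. A statement that no adverse events occurred would rest on incidental capture, and a single reported illness could not be interpreted without knowing what was meant to count.

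**Working it through.** **Figures in the plan.** The article gives no adverse-event rate, threshold or precision, so there is none to reproduce. The number at risk comes from Sample size calculation: 108 / (1 − 0.10) = 120, or 60 per group, which agrees with the text. Completers at 10% dropout: 108 / 2 = 54 per group.

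**Hypothesis against measurement.**

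| Part of the hypothesis | Measure in Feasibility | Post-baseline row in Table 2 |
|---|---|---|
| Willingness | Completion, future interest, recommendation | Not needed |
| Compliance | Completion, attendance | Not needed |
| No adverse events | None | None |

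**What zero events would show, if all events were found.** The exact upper limit after 0 of n is 1 − 0.05^(1/n) one-sided, or 1 − 0.025^(1/n) two-sided.
- n = 60: 1 − 0.05^(1/60) = 4.9%; 1 − 0.025^(1/60) = 6.0%.
- n = 54: 5.4% and 6.6%.

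These limits need no assumed rate.

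**How likely zero is.** P(0 events) = (1 − p)^60, where p is the 9-month risk per participant. The documents give no p, so the range is assumed:

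| p | P(0 in 60) |
|---|---|
| 0.1% | 94% |
| 0.5% | 74% |
| 1% | 55% |
| 2% | 30% |
| 3% | 16% |
| 5% | 4.6% |
| 10% | 0.2% |

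The chance falls below one half once p exceeds 1 − 0.5^(1/60) = 1.15%. The upper rows suit rare programme-related harm; the lower rows suit events of any cause.

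**Effect of incomplete capture (illustration).** If only a share c of events is noticed, the chance of recording none is (1 − cp)^60. Take p = 5%. With c = 1 it is 0.95^60 = 4.6%. With c = 0.4, cp = 2% and the chance is 30%. With c = 0.2, cp = 1% and it is 55%. The shares are assumptions; the article gives nothing from which to set c.

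**Link to completion.** Each intervention participant withdrawn for an adverse event also counts against completion. If the denominator is 60, each lowers it by 1/60 = 1.7 percentage points.

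**The case against.** The strongest reply has four parts.

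- **There is a recording route.** Withdrawal for adverse events, combined with documented and reported dropout reasons, captures some events after baseline in both arms. This stands. A reader might infer that the hypothesis would be confirmed simply by not looking; the text does not support that. What it supports is that no scheduled or systematic ascertainment is described.
- **It is a hypothesis, not a decision rule.** This also stands. A reader might infer that one unrelated illness would force a verdict of infeasible, but the Feasibility section sets no pass/fail rule on events. Nor do the documents show that zero is unrealistic: at assumed risks of 0.1% to 1%, zero in 60 has a 94% to 55% chance.
- **Articles condense.** How events are elicited and graded is commonly left to the full protocol. That is fair for procedure. It does not cover this point, because the article itself states the hypothesis, the feasibility measures and the schedule, and the latter two omit part of the first.
- **Differential capture between arms is conjecture.** It is tempting to argue that interactive sessions prompt more event reports than lectures. Nothing in the article shows this. Both groups are divided into teams, both have 9 months of sessions and 3 months of follow-up, and assessors are to be blinded. The point does not rely on it.

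**Conclusion.** The concern holds as a mismatch within the article: a primary hypothesis includes no adverse events, and neither the feasibility measures nor the schedule can establish it. Events after baseline reach the record only through withdrawal and dropout reasons, so a report of none would be ambiguous. Complete ascertainment of 0 of 60 would still leave a risk of up to 4.9% (one-sided 95%) or 6.0% (two-sided 95%) compatible with the data.

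The chance of meeting the hypothesis ranges from 94% to 4.6% over assumed risks of 0.1% to 5%; that spread reflects the missing definition of what counts. The calculation assumes independent participants with a common risk. The mismatch itself rests on no assumption. The point is worth correcting, but it does not touch the health-literacy primary outcome.

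**What to change.** 1. In the Background hypothesis, state whether all-cause or programme-related events are meant. Replace the expectation of zero with an estimate: the proportion of participants with any event, and with any serious event or new hypertension complication, by arm with 95% confidence intervals.
2. Add this measure to the Feasibility section. Add to Table 2 one standard event question and the existing complications item, asked identically in both arms at T1, T2 and T3. T1 and T2 cover the intervention period in the hypothesis; T3 covers follow-up.
3. Ask the same items at the point of withdrawal. Otherwise, participants withdrawn because of an event may not be present at the next visit to be counted.
4. Report the comparison descriptively. With one community per arm, community and treatment are fully confounded, so a difference in event proportions cannot be attributed cleanly to the programme.
5. Reconcile the Background hypothesis, the withdrawal provision in Recruitment and study population, the Feasibility measures, and Dropouts and missing data, and say how withdrawals for events enter the completion proportion.

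The cost is one or two questions at existing contacts, one extra results table, and a feasibility statement that will read less favourably than a bare claim of no adverse events.
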